## Abstract

**Background:**

The integration of a personal recovery-oriented practice in mental health services is an emerging principle in policy planning. Self-management support (SMS) is an intervention promoting recovery that aims at educating patients on the nature of their mental disorder, improving their strategies to manage their day-to-day symptoms, fostering self-efficacy and empowerment, preventing relapse, and promoting well-being. While SMS is well established for chronic physical conditions, there is a lack of evidence to support the implementation of structured SMS programs for common mental disorders, and particularly for anxiety disorders. This study aims to examine the effectiveness of a group-based self-management support program for anxiety disorders as an add-on to treatment-as-usual in community-based care settings.

**Methods/design:**

We will conduct a multicentre pragmatic randomized controlled trial with a pre-treatment, post-treatment (4-month post-randomization), and follow-ups at 8, 12 and 24-months.

**Treatment and control groups:**

a) group self-management support (10 weekly 2.5-h group web-based sessions with 10–15 patients with two trained facilitators); b) treatment-as-usual. Participants will include adults meeting DSM-5 criteria for Panic Disorder, Agoraphobia, Social Anxiety Disorder, and/or Generalized Anxiety Disorder. The primary outcome measure will be the *Beck Anxiety Inventory*; secondary outcome measures will comprise self-reported instruments for anxiety and depressive symptoms, recovery, self-management, quality of life, and service utilisation.

**Statistical analysis:**

Data will be analysed based on intention-to-treat with a mixed effects regression model accounting for between and within-subject variations in the effects of the intervention.

**Discussion:**

This study will contribute to the limited knowledge base regarding the effectiveness of structured group self-management support for anxiety disorders. It is expected that changes in patients’ self-management behaviour will lead to better anxiety management and, consequently, to improved patient outcomes.

**Trial registration:**

ClinicalTrials.gov: NCT05124639. Prospectively registered 18 November 2021.

## Background

### Background and rationale

Anxiety disorders are prevalent and disabling mental disorders characterized by marked fear, anxiety and avoidance behavior [1–3]. More frequent in women than men, they often appear during childhood and adolescence, and 50–80% of cases are comorbid with other anxiety disorders, mood disorders, and substance use disorders [4–7]. They also frequently coexist with chronic physical illness [8]. Individuals with anxiety disorders demonstrate significant psychological distress, functional and social impairment, suicide risk, and service utilization [1, 9–13]. The Global Burden of Disease Study ranks anxiety disorders as the sixth leading cause of years of life lived with disability [14]. Pharmacological and psychological treatments are recommended in clinical practice guidelines for the management of anxiety disorders [1, 15]. However, anxiety disorders often present a relapsing or chronic course [16–20], and residual symptoms are frequent, even among patients in remission [21, 22]. Thus, individuals have an active role to play in their lifelong recovery, beyond the contribution of evidence-based treatments, to develop self-management skills and improve functioning, prevent relapse and live a fulfilling life despite the presence of residual symptoms [23, 24].

Self-management support (SMS) is an intervention promoting recovery that aims at educating patients on the nature of their mental disorder, improving their strategies to manage their day-to-day symptoms, fostering self-efficacy and empowerment, preventing relapse and promoting well-being [25–27]. SMS is consistent with patient-centered care [28] and has the potential to enhance the efficiency of the health care system for patients by improving health outcomes and reducing overall service utilization [29]. SMS is a promising avenue towards recovery by fostering social inclusion, self-determination, autonomy, hope, and personal responsibility. Recovery is defined by the Mental Health Commission of Canada [30] as “living a satisfying, hopeful and contributing life, even when there are ongoing limitations caused by mental health problems and illnesses”. Previous studies have found that patients in recovery from anxiety disorders use a large variety of self-management strategies in their day-to-day life to foster their recovery [24, 31]. No less than 60 different self-management strategies have been identified in a qualitative study among patients in recovery from mood or anxiety disorders [31]. It is expected that changes in patients’ self-management behaviour will lead to better anxiety management and, consequently, to improved patient outcomes, relapse prevention, lower utilization of health care services, and cost savings. SMS typically offers a wide variety of self-management strategies that each person can draw upon based on their needs and preferences to make informed health decisions in their everyday lives, with a predominant focus on self-efficacy, active engagement in the long term, relapse prevention, peer support and facilitation approach. SMS interventions are positioned as a complementary intervention to evidence-based pharmacological or psychological treatments for anxiety disorders and offer a specific contribution to interdisciplinary mental health practice. While some overlap (e.g., psychoeducation, problem solving, relapse prevention) with low-intensity cognitive behavioural therapy (CBT) is acknowledged, a primary difference is that structured SMS programs tend to implement a holistic recovery-oriented approach centered on optimizing wellness and living a fulfilling life even in the presence of ongoing symptoms, to empower people to develop their very own self-management toolbox in a supportive framework, and to be provided by people with a large diversity of backgrounds (e.g., health care providers, social and community workers, peer supporters) [25].

While the value of the integration of SMS programs to health care services for chronic physical conditions is well-established [27, 29, 32] and rapidly growing for depression [25, 33–36], few studies have examined the added value of structured SMS programs for anxiety disorders as a complement to usual care. In a review by Houle et al. [25], the efficacy of SMS for depression was examined in six studies and promising results were observed for symptom reduction, self-management behaviours and self-efficacy, and mixed results for relapse rates. A recent literature search identified two other studies, conducted in the United States, that evaluated the efficacy of SMS group interventions, that were both peer-led and administered to heterogeneous samples of patients with mental health problems [34, 37]. While promising, most studies did not examine patient outcomes for anxiety disorders. Only two trials were found specifically for self-management support in anxiety disorders. In Germany, a cluster-randomised controlled trial of a nurse-led collaborative care intervention to promote self-management support has shown a small effect on self-efficacy in primary care patients with anxiety, depressive or somatic symptoms [38]. In the Netherlands, a randomized controlled trial evaluated a group rehabilitation and self-management program among patients with chronic anxiety and/or depression in an outpatient mental health care setting and reported a moderate effect on empowerment, but did not observe any significant effects on quality of life or symptom severity [39]. Consequently, there is a knowledge gap about the added value of structured SMS programs to usual care for common mental disorders, and particularly for anxiety disorders.

A program of self-management workshops for mental health has gathered interest from policy makers, health care managers, clinicians, and patients alike over the past few years. The *J’avance!* program was developed by a well-established mental health community-based organisation in Quebec, Relief (https://monrelief.ca), whose mission is to help individuals with anxiety disorders, depression, and bipolar disorder. The SMS program designed for anxiety disorders draws on personal recovery models as well as on low-intensity psychosocial and psychological interventions; it has been thoroughly developed in collaboration with researchers (JH; scientific lead) and reviewed by an interdisciplinary expert committee as well as participants from pilot groups. The SMS program covers a broad range of mental health intervention strategies (e.g., problem solving, emotion regulation, exposure, cognitive restructuring, mindfulness) and wellness-focused approaches (e.g., strengths, social support, lifestyle habits) in a non-directive “toolkit” aimed at building self-management skills. Great emphasis is placed on peer support, with participants sharing experiential knowledge, committing to trying self-management strategies and overcoming stigmatization. Since 2014, the SMS intervention was delivered over 445 times and over 1000 facilitators have been trained to date, and implementation is also beginning across Canada and internationally. Initially an on-site only workshop, Relief has implemented in 2020 a virtual delivery format on an eLearning platform and is now conducting group SMS workshops with both modalities. Given this wide-spread implementation, we sought to examine how the group SMS workshop translates into better mental health outcomes, health care system utilization and overall efficiency as a complement to usual care for patients with anxiety disorders.

### Objectives

The aim of the present study is to evaluate the effectiveness of a structured group virtual SMS program as an add-on to treatment-as-usual (TAU) in a sample of adults with anxiety disorders. Primary questions: When group SMS is added to TAU in community-based care for patients with anxiety disorders, is the SMS + TAU group more effective in reducing anxiety symptoms than TAU alone? Secondary questions: a) Considering a recovery-oriented approach for patients with anxiety disorders, is there a significant difference between group SMS + TAU and usual care in terms of self-management strategies and personal recovery assessment at the 12-month follow-up? b) Does group SMS + TAU present superior cost-effectiveness and cost-utility, in terms of quality of life and anxiety-free days, than TAU for patients with anxiety disorders at the 12-months follow-up? c) Is there a significant difference between group SMS + TAU and usual care for high-end functioning rates? d) Is there maintenance of gains at 12- and 24-months follow-up? e) Is there differential effectiveness based on moderators (i.e., sociodemographic characteristics, clinical characteristics, past treatment experience) and mediators (i.e., group cohesion, therapeutic alliance, adherence)?

### Trial design

The trial is a two-arm parallel group multicentre pragmatic superiority randomized controlled trial (RCT), with a 1:1 allocation at the individual level. The group SMS intervention will be offered to participants in the TAU groups after the 12-month follow-up (delayed-intervention). The 24-month follow-up will therefore only provide a within-group dataset. The proposed protocol conforms to SPIRIT guidance [40].

## Methods

### Participants, interventions, and outcomes

#### Study setting

The study will be conducted in four health administrative regions in Quebec (Canada): Eastern townships, Mauricie-et-Centre-du-Québec, Abitibi-Témiscamingue and Laurentides. Administrative regions were purposefully selected based on the following criteria: a) the in-person group SMS intervention is not currently largely implemented in the region; b) the virtual SMS intervention is rarely accessed by participants from the region, even though the virtual SMS format is technically accessible throughout the province; c) diversity (e.g., population size, region, university teaching hospital).

#### Eligibility criteria

This pragmatic RCT focuses on broad inclusion criteria for mixed anxiety disorders groups and minimal exclusion criteria. *Inclusion criteria:* (1) aged 18 and over, (2) fluent in spoken and written French, (3) meeting DSM-5 diagnostic criteria for at least one of the following anxiety disorders: Panic Disorder, Agoraphobia, Generalized Anxiety Disorder, and Social Anxiety Disorder, (4) access to a computer or tablet connected to the internet with microphone and video camera. *Exclusion criteria:* (1) previous enrolment in the SMS intervention for anxiety disorders provided by Relief, (2) active suicidal intentions, (3) severe depressive symptoms (i.e., PHQ-9 score ≥ 20), (4) active substance-related and addictive disorder, and (5) cognitive impairment.

#### Recruitment

Recruitment strategies will include self-referral following advertisements (e.g., waiting rooms of clinics, bulletin boards, geo-located website, and social media) and referrals from community-based primary care (e.g., family physician, community organization, mental health care team, mental health provider). The recruitment of participants will be conducted through a two-stage process. *Filter 1:* Self-referred individuals will acquire information on the study by accessing the study’s website or through a telephone call or email to our research laboratory. Self-referred individuals will complete a web-based screening survey comprising the required online consent form, basic eligibility criteria as well as anxiety symptoms and comorbidity overview. The initial web-based consent form and procedure has been approved by the ethics committee. At the end of the survey, they will provide their name and contact information. In the presence of clear exclusion criteria, a list of mental health resources will be provided. *Filter 2:* In the second stage (within 2 weeks of the screening survey), the baseline assessment will be conducted on a secure web-based platform with a trained clinical evaluator. The interview will begin with the consent form. The evaluator will explain the study, review the consent form with the participants, answer their questions, and verbally ask for their consent. The consent form will be sent by email for the participants to read prior to the online assessment, and this verbal consent procedure has been approved by the ethics committee given the web-based data collection method. The assessment will comprise sociodemographic data, service utilization and MINI International Neuropsychiatric Interview [41] for DSM-5 assessment (T_0_; random pre-assignment), combined with an adapted baseline Relief interview procedure (e.g., current main difficulties, interest in the program, capacity to use eLearning technology, readiness to take part in a group intervention). Patients meeting eligibility criteria at T_0_ will be given instructions to complete the remaining web-based self-reported questionnaires within 48 h, and only then will we have all required information to proceed with randomization. Figure 1 shows the study flowchart.

**Fig. 1 Fig1:**
[figure not shown]
Flow of participants

#### Interventions

##### Group SMS for anxiety disorders + treatment-as-usual (TAU)

The SMS manualized program for anxiety disorders (https://monrelief.ca) aims at improving self-management capabilities through weekly 2.5-h sessions with 10–15 patients over a 10-week period. The SMS program (see Table 1) covers the following themes: getting to know your anxiety; building self-awareness; reconsidering your lifestyle habits; adopting a problem-solving method; avoidance and exposure; acceptance and committed action; seeing things differently; managing your emotions; receiving support from others; and consolidating your toolkit. The trial will focus solely on the virtual format. As in the groups delivered by Relief, SMS will be either co-facilitated by health care professionals (e.g., social worker, psycho-educator, nurse), or by a health care professional and a peer supporter, namely a person recovered from an anxiety disorder who has experience and training offering peer support, building on mutual understanding and respect [42–44], to emphasize experiential knowledge sharing. *Relief* will provide the material for the training of the facilitators, the program documentation, the eLearning platform, and the material used by the participants. Consistent with standard implementation of this SMS program, facilitators will participate in a one-day *Relief* training program. Three case discussions for each group delivered (before onset, mid-group, and following last session) will be conducted by the research team. A random review of 30% of recordings of sessions will be conducted to monitor adherence with a treatment integrity scale. Integrity data will not be used to intervene to improve compliance, but only to examine process-outcome correlation and to guide improvements following the trial. Patient compliance will be supported through the extensive Relief experience delivering SMS (e.g., material, training, support), and the convenient eLearning platform (e.g., easy access, reduced stigma).

**Table 1 Tab1:** Content of the 10-week SMS manualized group program for anxiety disorders

Week	Theme	Content
1	Getting to know your anxiety	• Learn more about anxiety • Recognize the signs of anxiety
2	Building self-awareness	• Develop self-observation skills to better understand your anxiety • Understand the function of different resources that are available
3	Reconsidering your lifestyle habits	• Understand how lifestyle habits influence anxiety • Use an action plan to initiate change • Learn about mindfulness • Incorporate relaxation techniques
4	Adopting a problem-solving method	• Learn to put a problem-solving strategy into practice
5	Avoidance and exposure	• Understand how avoidance works • Learn the exposure technique
6	Acceptance and committed action	• Understand the acceptance process • Take action despite anxiety
7	Seeing things differently	• Become aware of filters (cognitive distortions) • Recognize and mitigate the negative effects filters have on anxiety
8	Managing your emotions	• Decipher the messages your emotions are sending • Become better equipped to manage your emotions
9	Receiving support from others	• Realize how anxiety influences interpersonal relationships • Appreciate the importance of social support • Expand your support network
10	Consolidating your tool kit	• Acknowledge your progress • Recognize and consolidate your new skills

##### Treatment-as-usual

No limitations will be imposed concerning usual care, as we aim at examining the added value of SMS to TAU. To reflect heterogeneity of health seeking behaviour and mental health practices for anxiety disorders in the community, we do not require that participants have a family physician, be constrained to a prespecified usual care or have contacts with the healthcare system. To minimize behavioural change in healthcare providers, we will not inform any healthcare provider of participation in the study. As the intervention will be provided on an eLearning platform, and not embedded in clinics, contact between intervention and control patients is unlikely. All participants will receive information about the SMS intervention and the goal of the study, i.e., “of helping them manage their anxiety”. We will thoroughly assess participant-reported service utilization 12 months prior to enrolment and during the study to examine risk of study-induced behavioral change with regards to usual care.

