#### Sample size

Due to challenges in calculations for mixed regression models [68], we estimated sample size based on the baseline (T_0_) and post-treatment (T_1_) difference between groups for the primary outcome. The sample size was calculated using G*Power with the BAI based on an estimated effect size of the SMS + TAU intervention (Cohen’s *d*) of 0.32 (0.56 intra-group). This corresponds to a 7-point difference based on previous studies [51] that have established *clinically significant change* thresholds for the BAI [69]; such an effect size at post-treatment for symptom reduction is consistent with previous SMS studies for mental disorders [25, 35, 37, 38] as well as with pilot data of SMS (conservative estimates). The 3-point difference and SD for the TAU only group are conservative values based on our current data in a similar study with a TAU group [70]. A sample size of 155 individuals per group is therefore required to detect a 4-point (pooled SD: 12.5) pre-post treatment difference between SMS + TAU and TAU (i.e., a 7-point difference for SMS + TAU and 3-point for TAU) with an 80% power and α = 0.05. As there is a potential for intraclass correlations (ICC) in an individually randomized group treatment trial [71], we also estimated [72, 73] that based on a mixed model accounting for possible between-individual correlations within each intervention group (ICC of 0.02 for based on a similar study [70]), the power would be of at least 76%. With an adjustment for a conservative 25% attrition rate, the proposed sample size is 207 individuals for each treatment arm.

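### The contamination statement does not address controls enrolling themselves in the public virtual SMS groups, and the service-use data as described do not name that exposure

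*Protocol article*

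**What the plan says.** All places are in the protocol article.

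- **Treatment-as-usual:** "No limitations will be imposed concerning usual care". All participants are told about the SMS intervention. Because delivery is online and not embedded in clinics, "contact between intervention and control patients is unlikely". Participant-reported service use is to be followed during the study to look for study-induced changes in usual care.
- **Study setting:** regions were chosen because in-person SMS is not widely implemented there and the virtual version is rarely used by residents, "even though the virtual SMS format is technically accessible throughout the province".
- **Trial design:** SMS "will be offered to participants in the TAU groups after the 12-month follow-up (delayed-intervention"). The section on participant timeline lists this delayed access among the retention incentives.
- **Eligibility criteria:** earlier enrolment in the organisation's SMS programme for anxiety disorders is an exclusion. Enrolment after randomisation is not mentioned.
- **Recruitment:** the baseline interview covers interest in the programme, ability to use the eLearning technology and readiness for a group.
- **Service utilization:** provincial databases supply medical and public psychosocial services, hospital stays and medication. A brief questionnaire at each assessment covers other mental health consultations and psychotropic medication.
- **Sample size:** "A sample size of 155 individuals per group is therefore required", on a 4-point difference, with a later adjustment for attrition.

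**The concern.** The trial tests only the virtual format, and that format is the one residents of the trial regions can reach through the organisation itself. A control needs no contact with an intervention participant to sign up. Online delivery, which the plan cites as protection, is also what makes self-enrolment possible. The statement on contact between arms therefore does not bear on this route.

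If some controls take SMS before an assessment, the intention-to-treat difference at that assessment shrinks towards zero. Without a record of who was exposed, a null result could not be told apart from dilution. In the economic evaluation, unrecorded SMS use by controls would also leave its cost out of the TAU arm. Exposure that is not collected during follow-up cannot be supplied by the analysts afterwards.

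**Working it through.** **Inputs (Sample size section, except group size and programme length, which come from Interventions).** Difference and spread: "required to detect a 4-point (pooled SD: 12.5) pre-post treatment difference between SMS + TAU and TAU", so d = 4/12.5 = 0.32. Error rates: "with an 80% power and α = 0.05" (sidedness is not stated; two-sided is assumed because it reproduces the figure). Attrition is 25%, ICC 0.02, group size 10–15, programme length 10 weeks.

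**Step 1: reproduce the plan's figure.**

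n per arm = 2(1.960 + 0.842)² × 12.5² / 4² = 153.3, so 154 by the normal formula. The two-sample t-test gives 154.3, so 155. Then 155/0.75 = 206.7, so 207. Both stated figures reproduce.

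**Step 2: reproduce the power with clustering.** With clustering in the SMS arm only and a mean group size of 12.5:

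- design effect = 1 + (12.5 − 1) × 0.02 = 1.23
- SE = 12.5 × √(1.23/155 + 1/155) = 1.499
- power = Φ(4/1.499 − 1.960) = Φ(0.708) = 76%

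This agrees with the stated 76%. Neither calculation contains an allowance for SMS uptake among controls.

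**Step 3: dilution.** The documents give no crossover rate. Let c be the assumed share of controls who take SMS before the assessment and gain its full effect, with the SD unchanged. The intention-to-treat difference is then 4(1 − c). With 155 evaluable per arm:

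| c (assumed) | Difference (points) | d | Power, no ICC | Power, ICC 0.02 | Evaluable n per arm for 80%, no ICC (randomised at 25% attrition) |
|---|---|---|---|---|---|
| 0% | 4.0 | 0.32 | 80.2% | 76.0% | 155 (207) |
| 5% | 3.8 | 0.304 | 76.1% | 71.7% | 171 (228) |
| 10% | 3.6 | 0.288 | 71.5% | 67.0% | 191 (255) |
| 20% | 3.2 | 0.256 | 61.3% | 56.9% | 241 (322) |

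**Step 4: which time point is exposed.** T1 is 4 months after randomisation, about 4 × 52/12 = 17.3 weeks. To finish a 10-week group by then, a control must start within about 7 weeks of randomisation. For T3 the same sum is 52 − 10 = 42 weeks. Later or partial attendance would dilute by less than the table shows. The primary comparison therefore has a narrow window, and the 12-month clinical and economic comparisons a wide one.

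**The case against.** The strongest reply is that the plan has already dealt with self-enrolment by choosing regions where the virtual programme is rarely used. The guaranteed offer after 12 months also weakens the motive to look elsewhere. In a pragmatic trial with unrestricted usual care, whatever controls find in the community belongs to the comparator. Questionnaire items are normally set out in case report forms, which an article need not show.

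Much of this stands, and it rules out several things a reader might infer:

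- **That the plan overlooks self-enrolment altogether.** It does not: the regional selection bears directly on it. But past regional uptake describes residents who had not been recruited, informed, interviewed about interest and then allocated to wait.
- **That no record would exist.** Service use is followed at each assessment and a control might mention a workshop. What can be said is narrower: the questionnaire is described in terms of consultations and medication, and a community workshop is not named.
- **That the Trial design and Treatment-as-usual sections contradict each other.** One says when the trial will offer SMS; the other says usual care is not restricted. Both can hold.
- **That controls can join at any moment in the 12 months, or had sought the programme.** The article says only that the virtual format is technically accessible. It gives no capacity or start dates. Participants are recruited to a study, through advertisements and referrals.
- **That the 24-month results are affected in the same way.** That follow-up is declared within-group only.

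What remains is that the stated argument does not cover the route, and the exposure is not named among the data to be collected.

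**Conclusion.** The point holds as an inexpensive improvement, not as a demonstrated bias. The route is open on the document's own description, and the reassurance given addresses a different one. The documents do not allow its size to be estimated. The figures of 3.8 points and about 76% power (72% with the ICC) at 5% uptake, and 3.6 points and about 72% (67%) at 10%, rest on assumed uptake, full benefit for every control who crosses over, and an unchanged SD. For the primary result at T1 they apply only to controls who join early enough, so they are likely to overstate the effect there for a given total uptake over the year. The T3 and cost-effectiveness comparisons are more exposed. The sample size itself is correctly calculated and need not be changed on this ground.

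**What to change.** 1. Add one explicit item on enrolment in the organisation's SMS groups outside the trial, with dates and sessions attended, to the questionnaire already given at T1, T2 and T3, in both arms.
2. With participants' consent, match the trial list against the partner organisation's registrations at the same points. The organisation is already a full member of the research team.
3. Report this exposure by arm, and count the cost of SMS taken by controls in the TAU arm of the economic evaluation.
4. State that such enrolment is part of unrestricted usual care for the intention-to-treat analysis, which stays primary, and is treated as crossover only in a sensitivity analysis.
5. For that analysis, estimate a complier-average effect with randomisation as the instrument: the intention-to-treat difference divided by the difference between arms in the proportion exposed. In the Step 3 illustration, with everyone in the SMS arm exposed, 4(1 − c)/(1 − c) returns 4 points. It assumes that allocation affects the BAI only through SMS attendance, which should be said plainly because participants are not masked and the outcome is self-reported.

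The cost is a consent line, one questionnaire item, a list match and one extra analysis. The downside is that registration data must be shared under consent. No one's care is restricted and the pragmatic design is unchanged.
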